### Ethical considerations

The researchers must obtain the approval of the study protocol and informed consent from the ethics committee. Meanwhile, researchers will be responsible for regular reporting as required by the institutional committee over the whole study period.

Any protocol amendments as well as associated informed consent changes will be submitted to ethics committee and written approval must be obtained prior to implementation. The informed consent form should be resigned when any modifications to the protocol happened.

Regarding the enrolled patients, we must obtain the informed consent signed by them in advance. The privacy of patients will be kept in strictly confidential during and after the TIGER study. All questions of privacy and secrecy are listed in the informed consent form (ICF). Enrolled patients have the right to withdraw from the trial anytime during the process of the study. All data will only be accessed by the study staff and kept strictly confidential. Patient data will be protected by locked cabinets at the Clinical Centers, and use of passwords limited access storage of electronic data.

Independent data monitor committee (IDMC) will be notified of all serious adverse events and unanticipated adverse device events occurring during the study. IDMC will also review compiled adverse event data at periodic intervals and report to the ethics committee any safety concerns and recommendations for suspension or early termination of the trial.

### Study organization

The TIGER study is a multicenter, prospective, randomized, open-label, controlled study designed and initiated by Tongren Hospital affiliated to Shanghai Jiaotong University Medical College. Doctor [name] is the principal investigator. We guarantee to obtain the informed consent and approval of the ethics committee before starting any research procedure. This study will compare the safety and efficacy of low- and standard- dose ticagrelor combined with aspirin in ACS patients 1 week after undergoing successful PCI with DES. The executive committee will be responsible for the scientific operational of the study. The independent data monitoring committee (IDMC) will be responsible for reviewing the data on a regular basis and determining the safety scope of the test, as well as the termination of the test, and the executive committee will finally decide whether to terminate the study ahead of time based on the recommendation of IDMC. The study will fully follow the ethical principles of the Helsinki declaration.

There is a sponsor that is separate from the funder and the sponsor and funder are independent. All data will be collected in case report forms (CRFs) and will be entered into electronic record form by two independent researchers to ensure the accuracy of the data. The data collectors will be trained to fill out the CRFs to ensure the accuracy of the data. Study staff will keep in touch with the participants every month by calls and encourage participants to see specialized research clinics when they have any concerns about their health conditions or the study. All data will be collected in case report forms (CRFs) and will be entered into electronic record form by two independent researchers to ensure the accuracy of the data. The missing data will be filled using the last observation carry-over method. We plan to publish the trial results in peer reviewed journal. Readers who want to check the original data can contact the corresponding author.

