### Sample size calculation

In our study, we assume that the composite of MACCE (defined as a composite of all-cause death, myocardial infarction, or stroke at 12 months after PCI) in the control group will be 5% at 1 year in ACS after PCI according to previous studies (STOD-DAPT2, RESET) [18, 19] The inferiority margin was set to 2.5% with clinical considerations. The sample size of the study should not be smaller than 1880 (940 per group) to guarantee 80% power of the study at one-sided significance level of 0.05. Considering 10% of the patients would be lost in the follow-up period, we determined the final sample size to be 2090 patients (1045 per group).

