### Statistical analysis

The efficacy analysis for primary endpoint will be performed in the intent-to-treat population, safety endpoints analyses will be performed in the safety analysis population.

The primary endpoint between groups will be compared with the use of logistic regression, adjusted for the stratification factors (ACS, age, sex, and diabetes). Odds ratio (OR) and the corresponding confidence interval (CI) will be estimated. If the upper limit of the two-sided 90% CI of the OR was less than the prespecified non-inferiority margin, low-dose DAPT strategy will be considered non-inferior to standard DAPT strategy in 1-year period after PCI in ACS patients. Besides, cumulative event rates will be estimated with the Kaplan-Meier method. Patients who were lost to follow-up were censored at the time of the last known contact.

Continuous variable will be descripted as mean (std) or median (interquartile range) as appropriate; categorical variables will be descripted as counts and percentages. *P* values and CIs were 2-tailed except those for non-inferiority testing of the primary end point.

No interim efficacy analysis is planned in this study, an independent data monitor committee (IDMC) will be set up to assess the safety of subjects periodically as previously described.

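### The carry-forward rule for missing data is not kept away from the primary endpoint: in the 1-year logistic model it codes patients lost before an event as event-free, while the Kaplan-Meier rates censor the same patients

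*Protocol article*

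**What the plan says.** All the relevant text is in the Methods of the protocol article.

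- **Study organization**, in the paragraph on data collection: "The missing data will be filled using the last observation carry-over method". No variable, endpoint or analysis is named or exempted. It is the only imputation rule in the article.
- **Statistical analysis**, primary test: "The primary endpoint between groups will be compared with the use of logistic regression, adjusted for the stratification factors". The population is intention-to-treat: "The efficacy analysis for primary endpoint will be performed in the intent-to-treat population". Non-inferiority is judged on the odds ratio (OR): "If the upper limit of the two-sided 90% CI of the OR was less than the prespecified non-inferiority margin".
- **Statistical analysis**, directly afterwards: "Besides, cumulative event rates will be estimated with the Kaplan-Meier method", and then "Patients who were lost to follow-up were censored at the time of the last known contact".
- **Sample size calculation**: "Considering 10% of the patients would be lost in the follow-up period", which raises 940 evaluable patients per group to 1045.

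Under Outcomes, the primary endpoint is a composite of events occurring within 1 year of the intervention.

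**The concern.** For an endpoint of the form 'any event by 1 year', the last observation on a patient who leaves event-free is 'no event'. Carrying it forward asserts that nothing happened for the rest of the year. A logistic regression of 1-year status needs a yes or no for each patient and has no means of using a censoring time. The censoring sentence therefore cannot supply the outcome in the primary model, and the carry-forward sentence can.

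Two things follow. The confirmatory test and the Kaplan-Meier rates would treat the same patients differently and could give different pictures, with nothing to say which governs. And the error rate of the non-inferiority claim would depend on how many patients are lost in each arm and when. Neither is under the trial's control, and the article specifies neither. The trial is open-label, so unequal loss is possible, although nothing in the article predicts its direction.

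**Working it through.** **Inputs from the article.** Control rate 5% at 1 year; margin 2.5%; one-sided 0.05; 80% power; 940 per group evaluable; 10% loss; 1045 per group randomised, 1:1.

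**Assumptions not in the article.** How loss splits between the arms; its timing; that loss is unrelated to risk; and, for the OR scale, a margin obtained by converting 2.5 points at a 5% control rate: (0.075/0.925)/(0.05/0.95) = 1.54.

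**Step 1: reproduce the design.** Reading the margin as an absolute risk difference (RD), n = (1.645 + 0.842)² × 2 × 0.05 × 0.95 / 0.025² = 940 per group, or 1880. Then 940/0.9 = 1044.4, rounded up to 1045 per group, or 2090. Both stated figures reproduce.

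**Step 2: events hidden.** 10% of 2090 is 209 patients. At a 5% rate, carry-forward hides about 209 × 0.05 = 10 events if all loss is at the start, and about half that (5) if loss is spread over the year.

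**Step 3: type I error.** Set the truth at the margin: 5% control, 7.5% low dose. An event before loss is kept, so the observed rate is p × (1 − loss × f), with f = 0.5 for loss spread over the year and f = 1 for loss at the start. The chance of declaring non-inferiority, with n = 1045 per group and without covariate adjustment, is:

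- RD scale: Φ((0.025 − RD)/SE − 1.645), SE² = p₀(1−p₀)/n + p₁(1−p₁)/n
- OR scale: Φ((ln 1.54 − ln OR)/SE − 1.645), SE² = 1/(n p₀(1−p₀)) + 1/(n p₁(1−p₁))

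Worked case, 10% lost in each arm, spread over the year: p₀ = 0.05 × 0.95 = 0.0475 and p₁ = 0.075 × 0.95 = 0.07125.

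- RD = 0.02375, SE = 0.01033; Φ(0.121 − 1.645) = 0.064.
- OR = 1.538, SE = 0.189; Φ((0.4321 − 0.4307)/0.189 − 1.645) = 0.051.

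| Lost, control / low dose | Timing | Observed rates | RD, points | OR | Type I, RD | Type I, OR |
|---|---|---|---|---|---|---|
| none | – | 5.00 / 7.50 | 2.50 | 1.541 | 5.0% | 5.0% |
| 10% / 10% | spread | 4.75 / 7.13 | 2.38 | 1.538 | 6.4% | 5.1% |
| 10% / 10% | early | 4.50 / 6.75 | 2.25 | 1.536 | 8.1% | 5.2% |
| 8% / 12% | spread | 4.80 / 7.05 | 2.25 | 1.504 | 8.0% | 6.4% |
| 8% / 12% | early | 4.60 / 6.60 | 2.00 | 1.466 | 12.6% | 8.3% |
| 5% / 15% | spread | 4.88 / 6.94 | 2.06 | 1.455 | 11.1% | 9.0% |
| 5% / 15% | early | 4.75 / 6.38 | 1.63 | 1.365 | 22.0% | 15.4% |
| 15% / 5% | spread | 4.63 / 7.31 | 2.69 | 1.627 | 3.4% | 2.7% |
| 15% / 5% | early | 4.25 / 7.13 | 2.88 | 1.728 | 2.2% | 1.3% |

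**Step 4: simulation check** (20,000 runs, loss uniform over the year). With carry-forward, type I error on RD and OR was 6.6% and 5.2% (10/10), 11.6% and 9.4% (5/15), and 3.6% and 2.7% (15/5), in line with the table. In the same runs a Kaplan-Meier risk difference that censors at last contact gave 5.2%, 5.4% and 5.0%, close to nominal under all three patterns.

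**The case against.** The strongest reply has four parts.

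- **The two rules may not collide.** The censoring sentence directly follows the Kaplan-Meier sentence and reads naturally as its rule. Carry-forward appears in a data-handling paragraph that names no endpoint. A reader might infer a flat contradiction, but the text does not establish one. What stands is that the carry-forward rule has no limit, the primary model cannot censor, and nothing says which rule applies there. That carry-forward feeds the primary model is an inference, though it is the only stated rule that could.
- **Not every lost patient is recoded.** A reader might infer that all lost patients become event-free. Those with an event before loss keep it.
- **Bias toward non-inferiority is not general.** A reader might infer it from the usual argument that erased events shrink differences. On the OR scale that the article names, equal loss changes almost nothing, and heavier control-arm loss works against non-inferiority. The larger RD figures matter because the 2.5% margin reproduces the sample size on that scale. The mismatch between that margin and an OR test is a separate matter.
- **The 10% is a planning allowance.** That it is twice the assumed event rate does not show that the rule would decide the result; about 5 to 10 events would be hidden. The 22% figure needs a threefold imbalance with all loss at the start, which monthly telephone contact makes unlikely.

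A further defence, that such detail belongs in an unseen analysis plan, does not apply: the article does not leave the rule open, it fixes one, and the rule is unsuitable for this endpoint.

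**Conclusion.** The point holds in conditional form. As written, an unrestricted carry-forward rule is the only one that gives the primary logistic model an outcome for patients lost before an event, and it codes them event-free. The Kaplan-Meier rates handle the same patients by censoring, and the article leaves this unreconciled.

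The consequence is an error rate governed by the loss pattern. It is near nominal on the OR scale if loss is equal, moderately raised on the RD scale, clearly raised on both if the low-dose arm loses more, and below nominal on both under the 15%/5% split. The documents do not support a claim that the trial is biased toward non-inferiority whatever the pattern. The figures rest on the assumed split, timing and non-informative nature of loss, and on the 1.54 conversion; the article gives only the overall 10%. This should be fixed, but it does not by itself invalidate the design.

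**What to change.** State that carry-forward does not apply to the primary endpoint, and name one rule for lost patients in the primary analysis. Either of these would do:

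- multiple imputation of 1-year status by arm and stratification factors, within the planned logistic model; or
- a 1-year estimate that uses censoring at last contact.

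Both treat loss as unrelated to risk given what is modelled, so add a tipping-point analysis that varies the event risk of lost patients in each arm and shows where the conclusion would change. Settle the rule before outcome data are analysed.

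The cost is a few sentences, a little more analysis work, and a confidence interval slightly wider than carry-forward would give.

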## Discussion

The introduction of second-generation drug-eluting stents and optimal medical therapy has significantly decreased the incidence of stent thromboses. Bleeding has gradually emerged as a predictor of early and late mortality in patients with ACS [3]. Therefore, avoiding bleeding events has become essential after using antiplatelet drugs for ACS patients undergoing PCI.

Previous studies have shown the advantage of short period of DAPT strategy in preventing ischemic events and reducing the risk of bleeding [7, 9, 18]. However, ACS patients usually present with concomitant diseases such as ischemic stroke and transient ischemic attack in which aspirin is essential for the secondary prevention. On the other hand, some small-scale studies showed that ticagrelor 60 mg bid achieved high peak levels through platelet inhibition in nearly all patients, similar to that of ticagrelor 90 mg bid [11, 20].

Therefore, we designed the TIGER study to compare the safety and efficacy of low-dose and standard-dose ticagrelor combined with aspirin in patients suffering from ACS after successful PCI. We believe the TIGER study will offer a good choice to find an optimal antiplatelet strategy for ACS patients after PCI.

## Trial status

Recruitment started on February, 2020, and is planned to end in February, 2022, with 2090 patients randomized. The current protocol version is 1.1, dated February 1, 2020.

## Data Availability

Not applicable.

## Abbreviations

ACS: Acute coronary syndrome
DAPT: Dual antiplatelet therapy
PCI: Percutaneous coronary intervention
DES: Drug eluting stent
IWRS: Interactive web response system
IDMC: Independent data monitor committee
CEAC: Clinical Event Adjudication Committee
